### 2.10. Data Collection Methods

All participating caregivers and children will complete a battery of measures at three points; one week pre-intervention (t1), two weeks post-intervention (t2), and six weeks post-intervention (t3), either electronically through Google Forms or conventionally through paper-based forms, as shown in Figure 3. At baseline, the Family Demographics Questionnaire (FDQ) will provide information on the age and gender of the caregivers, their marital, educational and work status, and the number of children they care for under the age of 16 years. In addition, caregivers will provide information on the age and gender of their children and their relationship to them. They will further provide information on their country of origin (if not Italy) and how long they have been living in Italy.

The Strengths and Difficulties Questionnaire (SDQ) is a 25-item behavioural screening questionnaire through which we intend to measure potential changes in children related to short-term impacts, such as “Improved child behaviour”, “Reduced aggressive and hostile behaviour”, and “Improved mental health in children”, as outlined in the logical framework (Figure 1). The 25 questions are summed to five subscales, ranging from 0 to 10 points (“Emotional problems scale”, “Conduct problems scale”, “Hyperactivity scale”, “Peer problems scale”, and “Prosocial scale” [Range: 10–0 points, with lower scores indicating lower prosocial skills]) and the “Total difficulties score”, ranging from 0 to 40 points, with higher scores indicating more problems. The SDQ showed good internal consistency of the Total Difficulties Score in 1394 Italian children aged 8–10 years [26].

Through the 30-item Parenting and Family Adjustment Scales (PAFAS) we intend to measure potential changes in caregivers related to short-term impacts, such as “Improved caregiver confidence in family management skills”, “Improved caregiving in parenting skills”, and “Increased capacity to cope with stress”, as outlined in the logical framework in Figure 1. The 30 questions are summed into 7 subscales, 4 parenting subscales (“Parental Consistency” [Range: 0–15], “Coercive parenting” [0–15], “Positive encouragement” [0–9], and “Parent-child relationship” [0–15]) and 3 family adjustment subscales (“Parental adjustment” [Range: 0–15], “Family relationships” [0–12], and “Parental teamwork” [0–9]). Higher scores on each of the scales mean worse outcomes; so, a decrease in scores after the intervention would mean a beneficial effect. The PAFAS subscales have shown good internal consistencies in two Australian samples (ranging from 0.70 to 0.87) and satisfactory construct and predictive validity [27].

Children are requested to fill in the 17-item revised Child and Youth Resilience Measure (CYRM-R), through which we aim to measure the short-term impacts, such as “Reduced aggressive and hostile behaviors”, “Increased capacity to cope with stress”, and “Improved mental health outcomes in children”. The CYRM-R comprises 2 subscales, the “Personal resilience subscale”, ranging from 10 to 50 points, and the “Caregiver resilience subscale”, ranging from 7 to 35 points. The overall scale is then summed out of the two subscales and ranges from 17 to 85 points, with higher scores indicating more resilience. The CYRM-R showed good overall fit statistics and a Rasch analysis indicated good psychometric properties for both subscales [28]. In our trial, we will use the 5-point version for youth aged 10–23 years with simplified language.

Children will further fill in the 14-item “Attitude Toward Interpersonal Peer Violence” (ATIPV) measure, with which we aim to measure “Reduced aggressive and hostile behaviors”, “Increased capacity to cope with stress”, and “Improved mental health outcomes in children”. A higher total score (summarised from each question ranging from 1 to 4 points) means a higher level of knowledge and skills in resolving conflicts non-violently. Through this measure, youth are asked to indicate their opinions or feelings about fighting (defined as physical fights, with pushing and hitting), not just arguments [29].

At t2 and t3, caregivers and children are requested to fill the SDQ, PAFAS, CYRM-R, and ATIPV again, making sure that the same caregiver and child complete the questionnaires at all time points (Figure 3).

All questionnaires will be merged through unique identifiers for each family.

Ten caregivers from each location will be invited to take part in interviews after completion of the Family UNited programme. The criteria for participation will be a randomised sampling of families. A semi-structured approach will be used to reduce the risk of missing any unanticipated issues and schedules; interview guides will provide a checklist of key areas of investigation, with prompts for guiding the interview. Topic areas will explore cultural acceptability, the efficacy of the programme against aims, barriers and facilitators to the engagement of the programme, key factors to adherence, and experience with recruitment.

For the process evaluation, all facilitators of the Family UNited programme will complete reflection sheets on recruitment, dose delivered, reach, staffing, and group size, following each programme session. Independent observers will complete checklists on the implementation of each of the sessions.

All English versions of the caregiver, child, facilitator, and observer questionnaires can be found in the Supplementary Materials; however, in the field, translations into Italian will be used. Previously-used translations have been used for the SDQ [30]; all other questionnaires were translated by bilingual Italian/English researchers for this trial.

### 2.11. Data Management

#### 2.11.1. Data Entry and Data Coding

All non-digital data will be entered electronically using R statistical software or EpiData and electronic data from Google Forms will be added. Analyses will be conducted using commercial statistical programmes, such as Excel, SPSS, STATA, R, etc. For identification purposes, names of the caregivers and children will be collected and will only be used by the research assistants during the intervention and data-collection phase. No identifying data will be entered or stored electronically. All data will be maintained in accordance with the Data Protection Act (1998).

The project managers in Italy, [name], [name], and [name], will be responsible for the storage of all digital and non-digital data. Interviews will be audio recorded (with participants’ and facilitators’ permission) using a digital voice recorder supporting file encryption. Notes will be written up as soon as possible following observation sessions and stored with transcriptions of the digital recordings. Identifying material will be removed as soon as possible from the transcripts and notes. Qualitative data will be copied into software files. Electronic copies of the transcripts will be held separately from the digital recordings of interviews and the file containing the participants’ names and corresponding numbers. Qualitative interviews will be conducted and transcribed in Italy; then, translated transcripts will be sent for analysis as encrypted files via electronic mail.

All non-digital data, such as sheets with participant identifiers, notes of the facilitators during the meetings, etc., will be immediately destroyed after the end of this study. All digital data (questionnaires and digitised interviews) will be kept for a maximum of 5 years at the University of Trento.

#### 2.11.2. Data Quality

Digital data entry will avoid entry errors caused by the researcher; although, it will not be able to eliminate the respondents’ compilation errors. Before the analyses, any out-of-scale values and the presence of missing data will be checked. A percentage of missing data greater than 30% will lead to the exclusion of the respondent from the analysis. Double entries will be checked using the options offered by Google Forms, as well as verifying the personal codes assigned to the participants.

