### 2.7. Sample Size

In the pilot study, 26 caregivers (17 in Parma and 9 in Trentino) completed the data collection before the intervention; whereas, only 18 caregivers (11 in Parma and 7 in Trentino) completed the data collection 2 weeks after the intervention. Overall, 19 children (11 in Parma and 8 in Trentino) completed both data collections. Based on the completion of both time points and excluding missing data, the following sample sizes were estimated. To keep the power at 80%, and to be able to show results for each of the scales, the sample size was calculated to be 40 participants in each group, resulting in a total number of families of 160, as shown in Table 4 and Figure 2.

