#### 2.11.3. Quantitative Statistical Methods and Qualitative Data Analysis

A mixed method approach using quantitative and qualitative measures will be used. Quantitative measurements will evaluate potential effectiveness, including a prospective collection of outcome data assessing changes in children’s behaviour, parenting skills, and family adjustment in caregivers. In addition, qualitative interviews will facilitate an understanding of the caregiver’s experience in taking part in the intervention and the cultural acceptability.

We will follow CONSORT guidelines for reporting and quantitative analysis. Statistical analysis will be undertaken by a researcher with relevant expertise and an analysis of quantitative measures will be conducted upon completion of the final measures, three months post-intervention.

All data will be analysed according to the intention to treat. Ideally, all participants will be followed up with, as has previously been performed. In case of a loss of follow-up or not all questions being answered, a non-responder analysis will be performed and those who did not attend a follow-up will be compared to the remaining. Missing data will be excluded from the analyses or imputed using the serial mean, depending on the amount of missing data.

The normality of the data distribution will be assured through a visual inspection of the histograms, Q-Q plots, and box plots. Cronbach’s alpha coefficients will be calculated to assess internal consistency.

For demographic data, continuous variables will be presented as means and standard deviations (SD), with a 2-sample *t*-test for comparison; whereas, categorical data will be summarised as frequencies and proportions and compared using a chi-square test. In case of non-normality, the respective non-parametrical tests will be used.

To compare scores at the different time points, we will conduct a two-way multi-level mixed ANOVA (time: within-subjects factor and group: between-groups factor), considering the subject and the territory random effects. This overall analysis will be followed by the simple effect analysis, if the interaction is significant, and by post hoc tests for the main effect of time, if significant, using use a method based on the false discovery rate (e.g., Holm’s correction), proportional to the size of the difference between the means.

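### The 30% respondent-exclusion rule has no stated denominator and conflicts with the intention-to-treat promise, and serial-mean imputation distorts either the effect or its standard error

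*Protocol article*

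**What the plan says.** Section 2.11.2 (Data Quality) sets the exclusion rule: "A percentage of missing data greater than 30% will lead to the exclusion of the respondent from the analysis". The section does not say whether the percentage is taken over items in a scale, one questionnaire session or all three sessions.

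Section 2.11.3 (Quantitative Statistical Methods) states the analysis principle: "All data will be analysed according to the intention to treat". For loss to follow-up and unanswered questions it plans a descriptive check, in which "a non-responder analysis will be performed and those who did not attend a follow-up will be compared to the remaining", and then gives the handling rule: "Missing data will be excluded from the analyses or imputed using the serial mean, depending on the amount of missing data". It does not say whether the mean is taken per arm, per visit or over everyone.

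For the main comparison the same section says "we will conduct a two-way multi-level mixed ANOVA (time: within-subjects factor and group: between-groups factor", with subject and territory as random effects. Section 2.10 fixes the schedule: "All participating caregivers and children will complete a battery of measures at three points".

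**The concern.** Intention to treat keeps each randomised family in the comparison with its allocated arm. A rule that removes a respondent because of what happened after allocation works against this, whatever its denominator.

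The stakes depend on how much is missing and why. Section 2.9 says that randomising schools before families are recruited may affect recruitment and dropout in the control arm, and everyone knows the allocation after baseline. Loss that differs by arm is therefore a risk the protocol itself recognises. Section 2.7 shows that loss can be large: of 26 pilot caregivers at baseline, "only 18 caregivers (11 in Parma and 7 in Trentino) completed the data collection 2 weeks after the intervention".

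Single mean imputation treats invented values as observed. Depending on which mean is used, it pulls the arms together or makes the standard error too small.

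**Working it through.** **Inputs.** Items: CYRM-R 17, ATIPV 14, SDQ 25, PAFAS 30 (section 2.10). Three waves. Pilot caregivers: 26 at baseline, 18 at two weeks (section 2.7). PAFAS parental adjustment: paired difference 1.2, SD 2.7 (Table 4). 160 families allocated 1:1, so 80 per arm. Alpha 0.05, taken as two-sided. Clustering is ignored throughout.

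**The plan's own figure.** Section 2.7 says "the sample size was calculated to be 40 participants in each group, resulting in a total number of families of 160". With the paired formula, n = ((1.96 + 0.84) × 2.7 / 1.2)² = 39.7, rounded up to 40. This reproduces the Table 4 entry at 80% power.

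**What one missed wave amounts to, if counted across waves.**
- Child (CYRM-R and ATIPV): 31 / (3 × 31) = 31/93 = 33.3%.
- Caregiver (SDQ and PAFAS): 55 / (3 × 55) = 55/165 = 33.3%. Attributing the SDQ to the caregiver is inferred from section 2.10, which names children only for the other two scales.
- If the baseline demographic form adds k items, the caregiver share is 55/(165 + k). It is 30.05% at k = 18 and 29.9% at k = 19. Section 2.10 lists about 11 pieces of information, giving 55/176 = 31.3%.

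On this count, a respondent with complete T1 and T2 who misses T3 is removed.

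**Cost in numbers.** Pilot loss is 8/26 = 30.8%. Carried over as an assumption, 160 × 18/26 ≈ 111 families remain, about 55 per arm. Two-arm power for 1.2 with SD 2.7 is Φ(√(n/2) × 1.2/2.7 − 1.96): 0.80 at n = 80 and 0.65 at n = 55.4.

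**Bias from exclusion.** If data are missing completely at random there is none. In one illustrative simulation (300 runs, assumed correlation 0.6 between waves), dropout before T3 depended on the T2 score in the intervention arm only, with 34% and 31% missing. For a true T3 difference of 1.2, exclusion gave 1.80 and a mixed model on all observed waves gave 1.18. The same mechanism analysed as change from baseline gave almost no bias (1.24 against 1.23 with full data). The size therefore depends on mechanism and estimand.

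**Mean imputation of whole scores, share m missing completely at random, equal in both arms.**
- Pooled mean: the effect is multiplied by 1 − m.
- Arm mean: the effect is unbiased, but the reported variance is (1 − m)σ²/n against a true σ²/((1 − m)n). The standard-error ratio is 1 − m, and type I error is 2(1 − Φ(1.96(1 − m))).

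| m | Pooled mean: 1.2 becomes | Arm mean: type I error |
|---|---|---|
| 5% | 1.14 | 0.063 |
| 10% | 1.08 | 0.078 |
| 20% | 0.96 | 0.117 |
| 30.8% | 0.83 | 0.175 |

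Simulation with 80 per arm and 10,000 runs, at 10%, 20% and 30.8% missing, agrees; at 30.8% type I error is 0.177, and 95% interval coverage is 0.82 under either mean when the true effect is 1.2.

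**Mean imputation of scattered items.** Assume a five-item scale, inter-item correlation 0.4, 80 per arm, and records above 30% missing removed. With 2% to 10% of items missing, pooled-mean filling turns 0.44 SD into about 0.44 to 0.41 SD, and arm-mean filling gives type I error of about 5% to 7% (6,000 runs).

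**The case against.** The strongest reply is that section 2.11.2 is about form quality: out-of-scale values, completion errors and double entries. In that setting the 30% may mean unanswered items on a submitted questionnaire, with loss to follow-up left to section 2.11.3. A reader might infer that a family missing one wave will certainly be deleted. The documents do not establish this, because no denominator is given. Even on the milder reading, however, randomised respondents are removed for post-randomisation missingness.

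A reader might also infer that a 31% shrinkage or an 18% type I error is to be expected. It is not. Those figures require whole missed waves to be mean-filled, and if the 30% is the cut-off, a missed wave would be excluded instead, whether counted across waves (33%) or within a wave (100%). Intermediate cases remain: counted across waves, one missed PAFAS is 30/165 = 18% of a caregiver's items, under the limit and open to mean-filling.

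Three further points stand. The wording in section 2.11.3 on excluding missing data can mean dropping only the missing observations, which in the planned model is sound. Mean imputation does keep participants in their arms, so its fault lies in the estimate or variance, not in breaking intention to treat. And the phrase about the amount missing may refer to the 30%, so a choice made after seeing the data is possible but not shown.

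The non-responder comparison deserves credit, but it describes selective loss and does not correct for it.

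**Conclusion.** The point holds in a limited form and should be fixed. The respondent exclusion conflicts with the stated intention-to-treat principle, and its missing denominator allows readings as far apart as occasional item non-response and every missed wave. On the across-wave reading, and with pilot attrition assumed to carry over, about 49 of 160 families would be lost and power would fall from 0.80 to 0.65 before clustering.

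It would be too strong to say that exclusion will bias the trial. Bias requires dropout related to arm and outcome; section 2.9 recognises dropout in the control arm as a risk, but the pilot has no arm-specific data.

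For mean imputation, the effect at 10% of whole scores missing is a factor of 0.90 or a type I error of about 8%. The 31% figures (0.69, about 18%) mark the worst case, and for scattered items the distortion is small.

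**What to change.** 1. Delete the respondent-level exclusion in section 2.11.2 and the serial-mean rule for scores in section 2.11.3.
2. State that every randomised family is analysed in its allocated arm, using the mixed model already planned, fitted by likelihood to all observed waves. This is valid if data are missing at random.
3. Apply any 30% threshold only to items within one subscale at one wave: prorate when no more than 30% are missing, otherwise set that score to missing and keep the respondent's other data.
4. Use multiple imputation by arm as a sensitivity analysis, and keep the non-responder comparison as a description.

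The cost is revised wording and a little more programming, with no new data. Section 4 says the trial has started, so the change should go through the amendment route in section 2.12.2 before outcome data are examined by arm.

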#### 2.11.3. Quantitative Statistical Methods and Qualitative Data Analysis

A mixed method approach using quantitative and qualitative measures will be used. Quantitative measurements will evaluate potential effectiveness, including a prospective collection of outcome data assessing changes in children’s behaviour, parenting skills, and family adjustment in caregivers. In addition, qualitative interviews will facilitate an understanding of the caregiver’s experience in taking part in the intervention and the cultural acceptability.

We will follow CONSORT guidelines for reporting and quantitative analysis. Statistical analysis will be undertaken by a researcher with relevant expertise and an analysis of quantitative measures will be conducted upon completion of the final measures, three months post-intervention.

All data will be analysed according to the intention to treat. Ideally, all participants will be followed up with, as has previously been performed. In case of a loss of follow-up or not all questions being answered, a non-responder analysis will be performed and those who did not attend a follow-up will be compared to the remaining. Missing data will be excluded from the analyses or imputed using the serial mean, depending on the amount of missing data.

The normality of the data distribution will be assured through a visual inspection of the histograms, Q-Q plots, and box plots. Cronbach’s alpha coefficients will be calculated to assess internal consistency.

For demographic data, continuous variables will be presented as means and standard deviations (SD), with a 2-sample *t*-test for comparison; whereas, categorical data will be summarised as frequencies and proportions and compared using a chi-square test. In case of non-normality, the respective non-parametrical tests will be used.

To compare scores at the different time points, we will conduct a two-way multi-level mixed ANOVA (time: within-subjects factor and group: between-groups factor), considering the subject and the territory random effects. This overall analysis will be followed by the simple effect analysis, if the interaction is significant, and by post hoc tests for the main effect of time, if significant, using use a method based on the false discovery rate (e.g., Holm’s correction), proportional to the size of the difference between the means.

Regression analyses (SEM) will also be conducted between the parental dimensions and the filial dimensions to evaluate the effect of parental change on the behaviour and emotional state of the child.

Stratified analyses will be conducted by gender, as well as for participants with worse scores (below the 33rd or above the 66th percentile) at baseline. Statistical significance will be set at a *p*-value lower than 0.05.

Qualitative data will be analysed using thematic analysis (TA) [31], where dominant themes will be identified through a close examination of the data. First, open coding will be carried out and an initial coding schedule will be devised in order to define each emerging theme. The coding manual will then be revised throughout the coding of the remaining transcripts. The original codes will frequently be combined or divided into further codes, depending on the emergent findings. Themes will be continually compared with newly coded interview transcripts to ensure that they are readily applicable to the data by using the research team’s familiarity with the text and coding manual to frequently assess and reassess how the codes are being applied to the raw data. The coding manual will be discussed within the research team and amendments will be made if necessary. The team will then develop a revised code set that includes the new and combined codes. NVivo9 software will be used to facilitate the analysis. The analysis will cease when the research team judges that thematic saturation has been reached [31].

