### 1.4. Objectives of This Study

The current study aims to explore the efficacy, fidelity, and acceptability of this universal prevention programme with families in Trentino and Parma, Italy and investigate the feasibility of delivering the programme.

The primary objective (impact evaluation) will be to test the efficacy of the Family UNited programme in improving family-skills outcomes and caregiver and child mental health and resilience, as reported by caregivers and children, when implemented in Trentino and Parma, Italy. According to the logic model of Family UNited (Figure 1), the short-term participant and family impact will be measured and compared against a waitlist/control group.

The secondary objective (process evaluation) will be to calculate the extent of families’ attendance to Family UNited sessions to evaluate the completeness of programme delivery. Further, the fidelity will be assessed to ensure facilitator compliance with the programme, as trained.

The tertiary objective will be to explore the cultural and contextual acceptability of the Family UNited programme for families in Trentino and Parma, Italy.

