### 1.5. Trial Design

To explore feasibility and ensure adequate implementation modalities, a pilot study was conducted in March/April 2022.

Subsequently, we plan to conduct a multi-site, non-blinded, 1:1 cluster-randomised controlled trial (cRCT) with two arms used to assess efficacy: the (1) intervention group (receiving the Family United programme) and (2) waitlist/control group (families only receiving the Family UNited programme after the completion of all data collection points).

We will prospectively collect all outcome data, assessing changes in parenting skills and family adjustment in caregivers, children’s behaviour, resilience capacities, and attitudes towards peer violence.

To assess programme delivery, fidelity, feasibility, and acceptability, we aim to include an embedded process evaluation.

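### The planned mixed ANOVA guarantees no baseline-adjusted arm difference at T2 or T3, and its post hoc tests on time cannot show efficacy against the waitlist

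*Protocol article*

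**What the plan says.** Section 1.4 sets the efficacy question as a comparison between arms: "the short-term participant and family impact will be measured and compared against a waitlist/control group". Section 1.5 describes a "multi-site, non-blinded, 1:1 cluster-randomised controlled trial (cRCT) with two arms used to assess efficacy". Section 2.10 places three measurements, the first before the programme and the others two and six weeks after it.

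Section 2.11.3 specifies a "two-way multi-level mixed ANOVA (time: within-subjects factor and group: between-groups factor"), "considering the subject and the territory random effects". All three measurements are levels of the time factor, and no baseline covariate is named. This overall analysis is then "followed by the simple effect analysis, if the interaction is significant, and by post hoc tests for the main effect of time", the latter also only if that effect is significant. The threshold is p below 0.05. The section does not say whether simple effects means arm at each time or time within each arm. It names no arm contrast at T2 or T3 as the efficacy result.

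**The concern.** There are three linked weaknesses.

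- **Baseline is a response.** No effect of the programme can exist at T1, so including that wave dilutes the group main effect. The interaction compares changes between arms. That is less precise than adjusting for the baseline score whenever the before-after correlation is below 1 and the SDs are similar.
- **The arm comparison is conditional.** Simple effects are examined only after a significant interaction. If it is not significant, the plan as written yields no estimate of the difference between programme and waitlist.
- **The time main effect averages over both arms.** It contains whatever happens to everyone, such as repeat testing or regression to the mean, including in families who only complete questionnaires. It cannot answer the question in section 1.4.

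At stake are some precision, an effect estimate that is always available, and a results section in which the between-arm comparison is the evidence.

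**Working it through.** **1. Degrees of freedom.** Three times and two arms give (3 − 1) × (2 − 1) = 2 for the interaction. The document does not print this.

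**2. The plan's own figure.** Table 4 gives Parental adjustment SD 3.1 before, 2.7 after, and a paired difference of 1.2 with SD 2.7. The paired formula n = ((1.96 + z) × 2.7 / 1.2)² gives 39.7 with z = 0.84 and 53.2 with z = 1.28. Rounded up, these are the printed 40 and 54. The inputs are therefore read correctly, and they are single-group before-after quantities.

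**3. Precision of the arm difference.** The implied correlation is r = (SD₁² + SD₂² − SD_d²) / (2 × SD₁ × SD₂). The baseline-adjusted variance is SD₂² × (1 − r²), and the change-score variance is SD_d². For Parental adjustment, r = (9.61 + 7.29 − 7.29) / (2 × 3.1 × 2.7) = 0.574. The adjusted variance is 7.29 × (1 − 0.330) = 4.89, and 4.89 / 7.29 = 0.67. With equal SDs the ratio is (1 + r)/2.

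| Scale | r | Adjusted / change score | Equal-SD form |
|---|---|---|---|
| Positive encouragement | −0.10 | 0.20 | 0.45 |
| Parental adjustment | 0.57 | 0.67 | 0.79 |
| Family relationships | 0.86 | 0.52 | 0.93 |
| Hyperactivity | 0.85 | 0.73 | 0.93 |
| Conduct problems | 0.63 | 0.37 | 0.81 |
| SDQ total | 0.70 | 0.73 | 0.85 |
| CYRM-R total | 0.93 | 0.91 | 0.97 |
| Personal resilience | 0.94 | 0.92 | 0.97 |

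The ratio is below 1 on all eight scales. Where the two columns differ widely, much of the gain comes from the pilot SD shrinking after the programme.

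For Parental adjustment with 80 per arm (160 families split 1:1, no clustering), the standard error is √(2 × 7.29 / 80) = 0.427 on change scores and √(2 × 4.89 / 80) = 0.350 adjusted.

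**4. Power of the planned sequence.** This was simulated for Parental adjustment with 80 per arm, 4,000 runs, compound symmetry, T3 SD equal to T2 SD, no dropout and no clustering. Simple effects were read as unadjusted arm comparisons. For both the gated plan and the adjusted analysis, the T2 and T3 comparisons were each tested at 0.025.

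| Effect (points) | Interaction alone | Interaction, then simple effect at T2 or T3 | Baseline-adjusted at T2 or T3 |
|---|---|---|---|
| 1.2 at T2 and T3 | 0.84 | 0.72 | 0.96 |
| 1.2 at T2 only | 0.85 | 0.66 | 0.88 |
| none | 0.05 | 0.007 | 0.05 |

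The last row confirms that the planned interaction test holds its level.

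**5. Illustration with clustering and dropout.** This is a 1-df comparison of T2 change, which is not the planned test. Retention is 18/26 = 69% (caregivers in the pilot, section 2.7), so 80 × 0.692 = 55.4 per arm. The ICC of 0.05 is an assumption. Cluster size is also assumed: 12 × 0.692 = 8.3 retained families, from the group size in section 2.3. The design effect is 1 + 7.3 × 0.05 = 1.365, and the standard error is √(2 × 7.29 / 55.4 × 1.365) = 0.600. Power for 1.2 points is 51% on change scores, and 61% (ratio 0.79) to 68% (ratio 0.67) with baseline adjustment. With 12 retained families per cluster the design effect is 1.55, and power is 47% rising to 56–63%.

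**The case against.** **The interaction already compares the arms.** It tests whether change differs between programme and waitlist, which is a fair reading of section 1.4. This stands, and any suggestion that the planned test is invalid would be wrong.

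**The 2-df test need not lose power.** A reader might infer that an omnibus test must be weaker than a 1-df test, falling from 80% to about 71%. That requires equal noncentrality. For Parental adjustment with 80 per arm, the 1-df T2 change test has noncentrality 1.44 / 0.182 = 7.90 (power 0.80). Under compound symmetry the interaction has 10.53 (power about 0.84) when the effect is sustained, and the same when it is present at T2 only. Equality arises only if the effect halves by T3, a pattern the documents do not state. The loss in this plan comes from the follow-up step and from not adjusting for baseline.

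**The size of the gain is uncertain.** With 14 pairs, r = 0.57 has a 95% interval of about 0.06 to 0.85, so the equal-SD ratio could lie anywhere from 0.53 to 0.92. The gain on the child-reported scales is small, and for a T2-only effect the adjusted analysis barely beats the interaction test alone (0.88 against 0.85). This stands.

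**Misuse of the time effect is not stated.** A reader might infer that the team will report a time effect as programme benefit. No sentence says so, and following up main effects is routine ANOVA wording. The CONSORT commitment in section 2.11.3 may also lead to intervals being reported, although no contrast is named for them. The risk is plausible, not documented.

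**Baseline adjustment is not only about precision here.** Section 2.9 accepts that randomising schools before recruitment can affect who enters. If baseline means then differ systematically, adjusted and change-score analyses can disagree. The choice should therefore be fixed in advance.

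**Conclusion.** The point holds as one of inefficiency and of a missing unconditional between-arm estimate. It does not hold as a type I error problem. The time main-effect tests are uninformative about efficacy whatever their result.

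The variance gain over change scores is about 33% for Parental adjustment (21% under equal SDs), 27% for SDQ total and 8 to 9% for the CYRM-R scales. The direction is secure on all eight Table 4 scales. The size is rough, because it rests on 12 to 14 pilot pairs, SDs rounded to one decimal, and the assumption that single-group pilot SDs apply to both arms. The 51% to 61–68% power figures are only an illustration for a 1-df T2 change-score test. They depend on an ICC of 0.05 and about 8 retained families per cluster, neither of which the documents give, and on 69% retention. This is a worthwhile change to the analysis, not a defect that invalidates it.

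**What to change.** In section 2.11.3:

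- Use T2 and T3 as responses in the mixed model, with arm, time, arm-by-time and the baseline score as a covariate. A longitudinal model that keeps T1 but constrains the arms to a common baseline mean would serve about equally well.
- Report the adjusted arm difference with a 95% CI at T2 and at T3, whether or not the interaction is significant.
- Name one of the two times as primary, or apply the Holm correction (already mentioned in that section) across the two.
- State that tests on the time main effect are descriptive and are not evidence of efficacy.

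How school and territory enter the model, and multiplicity across the many scales, are separate matters that this change does not settle.

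The cost is wording and some programming. The baseline scores are already collected and no extra data are needed. Section 4 says the trial has started, so the change should be dated and made before outcomes are examined by arm, and communicated as section 2.12.2 provides.
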